**Sampling, sample size and statistical power****Sample size determination:**

The design of the study is to compare the addition of PQ to AL or CQ alone. From our previous efficacy study, CQ alone showed a success rate of 68% at day 42 (null hypothesis). It will be assumed under the alternative hypothesis that the addition of PQ will decrease the chance of relapse by at least 60% resulting in a success rate of 87%. Group sample sizes of 97 in each group will achieve 90% power to detect a difference between group proportions of 19% using the two-sided Z-test with pooled variance test statistic. The significance level of the test was targeted at 0.05. Adjusting the alpha level to 0.025 for multiple comparisons will increase the sample size to 118 in each group. The AL arm showed even a lower efficacy at day 42 in our previous study of 58%. Using this lower success rate of 58% seen with AL at day 42, resulted in a smaller required sample size of 68. Taking into account 10-20% loss to follow-up at 42 days, a sample size of 120 subjects for each treatment was determined to be optimal.

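### 120 per arm covers either the adjusted alpha of 0.025 or the 10-20% loss to follow-up, but not both; power for CQ vs CQ+PQ is about 83-88%, not 90%

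*Protocol*

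**What the plan says.** All the figures are in one paragraph of the Protocol, under Sample size determination.

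- Assumptions for CQ: success of 68% at day 42 on CQ alone, and a reduction in relapse of at least 60% with PQ, giving 87%.
- Unadjusted size: "Group sample sizes of 97 in each group will achieve 90% power", "using the two-sided Z-test with pooled variance test statistic". On alpha: "The significance level of the test was targeted at 0.05".
- Multiplicity: "Adjusting the alpha level to 0.025 for multiple comparisons will increase the sample size to 118 in each group".
- AL: success of 58% on AL alone, which "resulted in a smaller required sample size of 68".
- Final size: "Taking into account 10-20% loss to follow-up at 42 days, a sample size of 120 subjects for each treatment was determined to be optimal".

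Under Data analysis plan, the per-protocol analysis drops patients who withdraw or are lost. A survival analysis keeps them until they leave.

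**The concern.** Read in order, the paragraph first adjusts for multiplicity (97 to 118) and then for loss (118 to 120). The second step adds two patients per arm, an allowance of 2/120 = 1.7%, whereas the loss named in the same sentence is 10-20%. The only base from which 120 accommodates that loss is 97, and using it discards the multiplicity adjustment made two sentences before.

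CQ vs CQ+PQ is one of the two primary comparisons under Efficacy end points. A reader would take it that this comparison has 90% power at two-sided 0.025 after the expected loss. If it does not, the chance of missing a true benefit of PQ is larger than planned, and the text does not show this.

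**Working it through.** **Inputs, from Sample size determination.** CQ success p1 = 0.68. CQ+PQ success p2 = 0.87, or 1 - 0.32 x 0.4 = 0.872 before rounding. Power 90%, two-sided pooled Z-test, equal groups, loss 10-20%, 120 enrolled per arm. The AL+PQ success rate is not printed. I assume the same 60% reduction: 1 - 0.42 x 0.4 = 0.832, rounded to 0.83.

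**Formulas.** With p = (p1 + p2)/2, A = sqrt(2p(1-p)), B = sqrt(p1(1-p1) + p2(1-p2)) and d = p2 - p1:

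- n per group = (z_alpha A + z_beta B)^2 / d^2
- power = Phi((d sqrt(n) - z_alpha A) / B)

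z_alpha = 1.960 at two-sided 0.05 and 2.241 at 0.025; z_beta = 1.282 for 90% power.

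**Step 1: reproduce the plan's figures.** For 0.68 vs 0.87, A = 0.5906, B = 0.5751 and d = 0.19.

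- Alpha 0.025: (2.2414 x 0.5906 + 1.2816 x 0.5751)^2 / 0.0361 = 117.6, so 118. This matches exactly, which shows that 118 is the evaluable number for 90% power with no loss allowance.
- Alpha 0.05: 99.4 with p2 = 0.87 and 97.0 with p2 = 0.872. Exact binomial enumeration of the pooled Z-test at 0.87 gives 90.05% power at n = 97. The printed 97 is sound.
- AL, 0.58 vs 0.83: 67.8 at alpha 0.05, which is the printed 68. At alpha 0.025 it is 80.3 (78.8 with 0.832), so 79-81 after rounding up. The 68 is therefore on the unadjusted alpha, although it follows the sentence that introduces the adjustment.

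**Step 2: apply the stated loss.** 120 x 0.9 = 108 and 120 x 0.8 = 96 evaluable per arm.

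**Step 3: CQ power at two-sided 0.025.** For example, at n = 96: (0.19 x 9.798 - 2.2414 x 0.5906)/0.5751 = 0.935, and Phi(0.935) = 0.825.

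| Evaluable per arm | Formula, 0.87 | Formula, 0.872 | Exact, 0.87 |
|---|---|---|---|
| 108 (10% loss) | 87.1% | 88.0% | 88.0% |
| 96 (20% loss) | 82.5% | 83.5% | 83.6% |

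Type II error is thus about 12-17.5%, up to about 1.7 times the planned 10%.

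**Step 4: what 120 does cover.**

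- At alpha 0.05: 97/0.9 = 107.8 and 97/0.8 = 121.3, so 108-122 enrolled. Power with 96-108 evaluable is 89.0-92.2% (formula, 0.87).
- At alpha 0.025: 118/0.9 = 131.1 and 118/0.8 = 147.5, so 132-148 enrolled.

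**Step 5: AL at alpha 0.025.** Power is 94.7% (0.83) to 95.1% (0.832) at n = 96, and 96.8% to 97.1% at n = 108.

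**Step 6: Holm over the two PQ comparisons.** They use different patients, so I treat them as independent. CQ is tested at 0.05 if AL is significant at 0.025, and at 0.025 otherwise. CQ power at n = 96 is 0.951 x 0.890 + 0.049 x 0.825 = 0.886; at n = 108 it is 0.971 x 0.922 + 0.029 x 0.871 = 0.921. With 0.872 the results are 0.894 and 0.927.

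**The case against.** The Protocol attaches 90% power explicitly only to 97 at alpha 0.05 and states no power for 120. On that reading 120 is the unadjusted design with loss added, and nothing was promised at 0.025. The first part is true, but it does not remove the problem. The adjusted 118 would then have been calculated and dropped without comment, in a paragraph that presents both adjustments as made.

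The planned survival analysis keeps patients until they drop out, so counting losses as zero information is pessimistic. This stands as a partial mitigation whose size cannot be computed from the document. The sample size, however, rests on a test of proportions, and the per-protocol proportions exclude lost patients. They also exclude withdrawals and unclassifiable PCR results, which work the other way.

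The 60% reduction is stated as a minimum. With a 65% reduction (success 1 - 0.32 x 0.35 = 0.888), power at alpha 0.025 is 90.4% at n = 96 and 93.6% at n = 108. This shows that the gap is modest, but the plan's own calculation uses 60%.

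The AL figure has no consequence for the final size, since both 68 and about 80 lie below 96. That is correct; it is a point of clarity only.

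Finally, a fixed split at 0.025 is valid, so Holm is not needed for correctness. That also stands.

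**Conclusion.** The sample size statement is wrong as written. With 120 enrolled per arm and the Protocol's own 10-20% loss, CQ vs CQ+PQ has about 83-88% power at two-sided 0.025. That is about 2 to 7.5 points below 90%. At alpha 0.025, 120 tolerates 1.7% loss.

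The result assumes 68% vs 87% (or 87.2%) success, a pooled Z-test of proportions, and no contribution from lost patients. None of the rounding choices or the exact calculation in the table brings power to 90%.

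The weight is moderate. One of two primary comparisons is affected, its power stays above 80%, and AL vs AL+PQ keeps about 95-97% if the same 60% reduction applies. Type I error is not affected, provided the 0.025 level is actually used; the paragraph leaves that unclear.

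**What to change.** Keep 120 per arm and correct the text under Sample size determination:

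- State the alpha at which the two PQ comparisons will be tested, and label each sample size with the alpha it uses.
- State that 10-20% loss leaves 96-108 evaluable per arm, with power at two-sided 0.025 of about 83-88% for CQ vs CQ+PQ and about 95-97% for AL vs AL+PQ.
- Give the AL requirement at alpha 0.025 as about 80 instead of 68, and print the assumed AL+PQ success rate.

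These are wording changes and need no extra patients.

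Optionally, replace the fixed 0.025 split with Holm's procedure over the two comparisons. It holds the family-wise error at 5% and gives CQ power of about 89-93%, provided the AL effect is as assumed. At 20% loss it still falls just short of 90%. It costs one line on the testing procedure.

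If 90% at a fixed 0.025 is required, the CQ arms need 132-148 enrolled each, which is 12-28 more per arm.

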### **Laboratory Evaluations:**

2. Urine pregnancy test will be conducted on all women aged 13-49 and anyone testing positive will be excluded.
3. Those enrolled will have a second finger prick performed to assess for the following:
  - Thin smear will be used to verify parasite species and thick smear to conduct a formal parasite count. Two qualified microscopists will read all the slides independently. Blood smears with discordant results (differences between the two microscopists in species diagnosis, in parasite density of > 50% or in the presence of parasites) will be re-examined by a third, independent microscopist, and parasite density will be calculated by averaging the two closest counts.
  - Hemoglobin measurement (HemoCue™ Hb 301HemoCue, Angelholm, Sweden) will be carried out and those with hemoglobin <8g/dL will be excluded.
  - Filter paper will be obtained for the purpose of genotyping to differentiate identical vs. different genotypes, potential molecular testing for resistance markers, and gametocyte testing. G6PD testing using the NADPH fluorescent spot test will be conducted at the end of each day. The NADPH fluorescent spot test is a qualitative test and those determined to be G6PD deficient will not be given primaquine.
4. Patients testing smear positive for Pv will receive AL, at one site and CQ at the other site. After G6PD testing results are available, the patients not found to be G6PD deficient will be randomized to either AL alone or AL+PQ at one study site and CQ alone or CQ+PQ at the other site. Those found to be G6PD deficient will remain in either the AL or CQ alone arms. The study will not be blinded, although microscopists reading blood films will not be aware of which arm a participant is from.
5. On day 0, each patient will receive the morning dose of treatment (AL or CQ) medication under direct observation and will be monitored for vomiting for 60 minutes. The patient or parent will be given the evening dose (for AL only) to administer at home. Each patient will return on days 1 and 2 (and up to 14 days for those in the PQ arms) for subsequent doses. Those in the primaquine arms will return on every second day on days 2-16 for directly observed therapy. Clinical reassessments will be made on days 1- 3, 7, 14, 21, 28, 35, 42, and then monthly (see Annex V and VI for a table of scheduled procedures).

Participants will be given 35 Ethiopian Birr for each visit to cover their travel expenses (this is

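### With 120 per treatment and the stated 10–20% loss, the CQ comparison has 82.5–87.1% power at alpha 0.025, not 90%, and the AL size of 68 rests on a different alpha

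*Protocol*

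**What the plan says.** The Protocol, Sample size determination, sizes the two primaquine comparisons separately.

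- **CQ versus CQ+PQ.** Success at day 42 is taken as 68% without PQ and 87% with it, from an assumed 60% fall in relapse. The first size is for the unadjusted test: "The significance level of the test was targeted at 0.05", giving 97 per group for 90% power with a two-sided pooled Z-test. The next sentence reads: "Adjusting the alpha level to 0.025 for multiple comparisons will increase the sample size to 118 in each group".
- **AL versus AL+PQ.** Success on AL alone is taken as 58%, which "resulted in a smaller required sample size of 68". Neither the alpha nor the AL+PQ rate behind this figure is given.
- **Final size.** Citing 10–20% loss to follow-up at 42 days, the section ends: "a sample size of 120 subjects for each treatment was determined to be optimal". With four treatments this implies 480 patients, a total the section does not print.

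**The concern.** The closing sentence presents 120 as a size that already allows for loss. It is only two above the 118 required before any loss, so it tolerates 1 − 118/120 = 1.7% loss, against the 10–20% the section expects. A reader would take it that both comparisons keep 90% power after loss and at the adjusted alpha. If that is wrong for CQ, the trial carries a higher risk than it states of missing the assumed primaquine effect with the country's first-line vivax drug.

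The sizes 118 and 68 also stand side by side as if they shared one alpha. If they do not, the section has no consistent basis for the two comparisons.

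**Working it through.** **Inputs** (Protocol, Sample size determination): CQ 68% versus 87%; AL alone 58%; 90% power; two-sided pooled Z-test; alpha 0.05 and 0.025; loss 10–20%; 120 per treatment. The AL+PQ rate is not stated. Applying the same 60% reduction to 42% failure gives 1 − 0.4 × 0.42 = 83.2%, taken here as 83%.

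**Formulas**, with p̄ the mean of the two rates and d their difference:

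n per group = [z(1−α/2)·√(2p̄(1−p̄)) + z(0.90)·√(p₁(1−p₁) + p₂(1−p₂))]² / d²

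power = Φ{[d√n − z(1−α/2)·√(2p̄(1−p̄))] / √(p₁(1−p₁) + p₂(1−p₂))}

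**1. Reproducing the plan's sizes**

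- CQ, alpha 0.025: [2.2414 × 0.5906 + 1.2816 × 0.5751]² / 0.19² = 4.246 / 0.0361 = 117.6, so 118. This matches.
- CQ, alpha 0.05: 100 from the rounded 87%, and 97 from the unrounded 1 − 0.4 × 0.32 = 87.2%. The printed 97 is accounted for.
- AL, alpha 0.05: [1.9600 × 0.6449 + 1.2816 × 0.6202]² / 0.25² = 4.239 / 0.0625 = 67.8, so 68. This matches.
- AL, alpha 0.025: [2.2414 × 0.6449 + 1.2816 × 0.6202]² / 0.25² = 5.020 / 0.0625 = 80.3, so 81 (79 with 83.2%).

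So 118 is at alpha 0.025 and 68 is at alpha 0.05. With 68 evaluable per group, AL power at alpha 0.025 would be 84.0%.

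**2. Adding the stated loss, n/(1 − loss)**

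| Evaluable needed | 10% loss | 15% loss | 20% loss |
|---|---|---|---|
| CQ 118 (alpha 0.025) | 132 | 139 | 148 |
| AL 81 (alpha 0.025) | 90 | 96 | 102 |
| AL 68 (alpha 0.05) | 76 | 80 | 85 |
| CQ 97 (alpha 0.05) | 108 | 115 | 122 |

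The chosen 120 is below the whole first row. It is close to 97/0.8 = 122, the size for the unadjusted alpha.

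**3. Power delivered by 120 enrolled per treatment, alpha 0.025**

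| Loss | Evaluable per group | CQ power | AL power |
|---|---|---|---|
| 10% | 108 | 87.1% | 96.8% |
| 15% | 102 | 85.0% | 95.9% |
| 20% | 96 | 82.5% | 94.7% |

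Example, CQ at 20% loss: (0.19 × √96 − 2.2414 × 0.5906) / 0.5751 = 0.935, and Φ(0.935) = 82.5%.

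**4. Sensitivity to rounding.** With 87.2% and 83.2%, CQ power is 88.0% at 10% loss and 83.5% at 20%, and AL power is 97.1% and 95.1%. CQ stays below 90% throughout.

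**The case against.** **At alpha 0.05 the number works.** CQ power with 120 enrolled is then 92.2%, 90.7% and 89.0% at 10, 15 and 20% loss. That stands, and it may be how 120 arose. But the section itself raises the requirement to 118 for multiple comparisons and withdraws that nowhere. If 0.05 is meant, the adjustment sentence has no effect.

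**Lost patients are not wholly lost.** The Protocol's survival analysis keeps them until drop-out, so its power may suffer less than shown here. But the size was computed for a test of two proportions, the section makes its own deduction for loss, and the per protocol analysis excludes these patients.

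**The stronger reading: that equal arms are the error.** Seeing 118 beside 68, a reader might infer that AL is over-recruited at the expense of CQ and that the implied 480 should be split, for example, 140 per CQ arm and 100 per AL arm. That split does give CQ 92.0 / 90.4 / 88.4% and AL 93.2 / 91.7 / 89.9% at 10 / 15 / 20% loss. The document does not show that it is required:

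- The contrast of 118 with 68 mixes alphas; like for like it is 118 with 81.
- Equal arms did not cause the CQ shortfall; the missing allowance for loss did. Equal arms are a legitimate choice.
- The gain depends on AL failing more often than CQ. The Introduction's counts, 47/113 and 34/107, differ by 9.8 points, with a 95% interval of about −2.8 to 22.5. If AL alone in truth succeeds in 68%, as CQ does, 100 per AL arm gives only 79.7 / 77.2 / 74.3%, against 87.1 / 85.0 / 82.5% with 120.
- Treating the comparisons as independent, the chance that both succeed rises by only about 1 point (at 20% loss, 0.825 × 0.947 = 78.2% against 0.884 × 0.899 = 79.4%).
- At 20% loss, 90% for both needs 2 × (148 + 102) = 500 patients, more than 480.
- Separate site targets presuppose Laboratory Evaluations, item 4: "Patients testing smear positive for Pv will receive AL, at one site and CQ at the other site". The section Intervention or treatment instead randomises all patients between AL and CQ. The two must be reconciled first.
- The AL patients also serve the 12-month recurrence, hemoglobin and adverse event comparisons.

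**Conclusion.** The sample size statement is wrong as written on two counts. First, the 118 was not inflated for the section's own 10–20% loss, so 120 per treatment gives the CQ comparison 82.5–87.1% power at alpha 0.025, a shortfall of about 3 to 7.5 points from 90%. Second, the AL size of 68 belongs to alpha 0.05, and its counterpart at 0.025 is 81. AL is not at risk: it keeps 94.7–96.8%.

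This rests on the plan's own rates, test and loss range, on the adjusted alpha applying to both comparisons, on lost patients not contributing to the day 42 test, and on an inferred 83% for AL+PQ. It does not follow that equal allocation is a mistake or that AL recruitment should be cut.

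**What to change.** In Sample size determination:

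1. State one alpha, 0.025, for both comparisons.
2. Give the AL size as about 81 per group at that alpha, with the assumed AL+PQ rate.
3. Keep 120 per treatment, and replace the claim that this is the best size after loss with the power it delivers: CQ about 87% at 10% loss and 82% at 20%; AL about 97% and 95%.

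The cost is a few sentences, with no added patients or procedures; the sponsor openly accepts less than 90% for CQ.

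Shifting recruitment targets from AL to CQ may be weighed as an option. It should come only after the two descriptions of how the drug is assigned have been reconciled, and with the AL power shown over a range of AL-alone success rates. It would widen the AL intervals and, if AL behaves like CQ, lower the weaker of the two powers.

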**SCREENING AND ENROLLMENT PROCEDURES****Screening Procedures for Enrollment**

Screening for eligible patients at the two study sites will be done in the following fashion:

1. All patients presenting to the evaluation sites will be registered. At malaria treatment centers all patients will get a blood smear, whereas at health centers all patients presenting with fever will then get a blood smear. Patients with microscopy confirmed diagnosis of Pv malaria illness, age greater than 1 year, and living within 20 km of the health center will be screened for eligibility for enrollment. Those patients who for any reason are not enrolled into this study according to the screening and enrollment process will be treated promptly according to the current National Malaria Diagnosis and Treatment Guidelines [1].
2. If the patient meets the screening criteria and the patient or the parent or guardian asked for permission consents to enrollment, they will be assigned a consecutive, unique number that will become the patient's study number and will be used to identify all forms and blood samples from that patient. Enrollment will be conducted by a staff member not involved in the clinical assessment of the participant to ensure that consent is freely given.

3. A screening form containing demographic, clinical, and laboratory information will be started on each smear positive patient, thus allowing for appropriate tracking of each patient through the screening procedure.
4. The patient's body weight will be measured, using a hanging scale for weighing young children, or a floor scale for large children/ adults and recorded on the demographic form.

### **Enrollment Procedures**

If a patient meets the initial screening criteria and permission to participate in the study is obtained, the patient will go through the enrolling process.

### **Clinical Evaluation:**

1. Patient will be evaluated by clinical staff for signs of febrile illness other than malaria, (including but not limited to pneumonia, otitis media, tonsillitis, measles, chicken pox, abscesses) and signs of severe disease/ danger signs, as presence of any of these will exclude the patient from participating in the study. Patients found to have any of these conditions will be treated appropriately per National Guidelines [1], or referred to the nearest health center if seen at a malaria treatment center. A standardized form listing demographic and clinical information will be completed on each patient.

### **Laboratory Evaluations:**

2. Urine pregnancy test will be conducted on all women aged 13-49 and anyone testing positive will be excluded.
3. Those enrolled will have a second finger prick performed to assess for the following:
  - Thin smear will be used to verify parasite species and thick smear to conduct a formal parasite count. Two qualified microscopists will read all the slides independently. Blood smears with discordant results (differences between the two microscopists in species diagnosis, in parasite density of > 50% or in the presence of parasites) will be re-examined by a third, independent microscopist, and parasite density will be calculated by averaging the two closest counts.
  - Hemoglobin measurement (HemoCue™ Hb 301HemoCue, Angelholm, Sweden) will be carried out and those with hemoglobin <8g/dL will be excluded.
  - Filter paper will be obtained for the purpose of genotyping to differentiate identical vs. different genotypes, potential molecular testing for resistance markers, and gametocyte testing. G6PD testing using the NADPH fluorescent spot test will be conducted at the end of each day. The NADPH fluorescent spot test is a qualitative test and those determined to be G6PD deficient will not be given primaquine.
4. Patients testing smear positive for Pv will receive AL, at one site and CQ at the other site. After G6PD testing results are available, the patients not found to be G6PD deficient will be randomized to either AL alone or AL+PQ at one study site and CQ alone or CQ+PQ at the other site. Those found to be G6PD deficient will remain in either the AL or CQ alone arms. The study will not be blinded, although microscopists reading blood films will not be aware of which arm a participant is from.
5. On day 0, each patient will receive the morning dose of treatment (AL or CQ) medication under direct observation and will be monitored for vomiting for 60 minutes. The patient or parent will be given the evening dose (for AL only) to administer at home. Each patient will return on days 1 and 2 (and up to 14 days for those in the PQ arms) for subsequent doses. Those in the primaquine arms will return on every second day on days 2-16 for directly observed therapy. Clinical reassessments will be made on days 1- 3, 7, 14, 21, 28, 35, 42, and then monthly (see Annex V and VI for a table of scheduled procedures).

Participants will be given 35 Ethiopian Birr for each visit to cover their travel expenses (this is

enough to cover round-trip transportation by bus to the clinic for one adult; parent traveling with the enrolled child requiring their own seat (age >6 years) will receive 50 Birr). Patients will be advised to return on *any* day during the follow-up period if symptoms return and not to wait for scheduled visit days (although they will not be reimbursed for extra visits unless found to be legitimate visits). Patients who do not present to the facility for follow-up visits will be followed at home. This is standard for in vivo studies based on the WHO protocol, but is not the standard for routine care. Typically, for patients not enrolled in a study, the patients would be given all the doses of the medicine to administer at home, and no follow-up would be scheduled. The patient would be told to return if the child did not improve.

6. Blood films (thick and thin) for parasite count will be obtained and examined at each visit and on any other day if the patient spontaneously returns with fever or worsening symptoms.

7. Hemoglobin status will be measured on days 0, 3, 7, 14, 28, 42 and any other unscheduled visits.

8. **Drug level testing.** DBS will be collected on day 7 for lumefantrine plasma level [39], day of recurrent parasitemia for chloroquine levels [40], and day 7 and 14 for primaquine levels. Drug level testing involves liquid chromatography and these tests will be conducted at CDC Atlanta.

9. **Molecular testing.** A filter paper blood spot will be collected on days 0 and after day 3 in case of recurrent parasitemia for an array of parasite molecular testing including genotyping, resistance drug markers, parasite genome sequencing, and for gametocytes. In *P. falciparum* malaria primaquine accelerates clearance of gametocytes and artemisinin derivatives prevent gametocyte development. However, in *P. vivax* malaria effect of these drugs on gametocyte carriage remains unclear due to limited studies. Therefore, we will examine gametocytemia by blood smear and measuring Pvs25 using reverse –transcript quantitative PCR tool in the smear positive DBS from day 0 and follow up visits. Lastly, for any patients noted to have G6PD deficiency or a greater than 2.4g/dL drop in hemoglobin, their DBS sample will be tested for genetic variants of G6PD deficiency. The molecular testing will be conducted in Addis Ababa, Ethiopia, by Ethiopia Health and Nutrition Research Institute (EHNRI). If EHNRI cannot accomplish this in a timely manner, CDC Atlanta, will serve as a back-stop institution. All samples will have the study ID number and date of collection, but no other personal identifiers. The logbook that links the study ID number to the patient will be kept at the study site locked in a cabinet when not in use during the study enrollment period. After the completion of the study, this logbook will be stored in a locked cabinet in Addis Ababa at ICAP’s office. DBSs will not be used for non-malaria-related tests including HIV.

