## **Intervention or treatment**

**Antimalarial Therapy-** All patients will be randomized to receive AL or CQ. Once G6PD results are available, those testing normal will be randomized to PQ or no PQ.. In Ethiopia G6PD deficiency is very rare (0.5-2.9%) [38]. All doses of CQ, PQ, and morning AL will be given under supervision by the staff. The evening dose of AL will be given to the patients to take at home. Children less than 5 years of age will be given an extra evening dose in case of vomiting. Patients will be observed for 60 minutes after treatment for adverse reactions or vomiting. Those patients vomiting their medication within the first 30 minutes will receive a repeat full dose, those vomiting from 30-60 minutes will receive half dose. This is standard practice for anti-malarial treatment.

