#### **Safety end points**

Change in hemoglobin concentration within 7 days of start of treatment in PQ compared to the no PQ arm. Hemoglobin concentration will be assessed on day 0, 3, 7, 14, 28, 42. All adverse events will be documented. The proportion of participants with solicited and unsolicited adverse events, overall and specific, will be compared between treatment arms. Events will be analysed in relation to time of the drug administration.

The classification of treatment outcomes will be based on an assessment of the parasitological and clinical outcome of antimalarial treatment according to the latest guidelines from WHO [41].

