## DATA HANDLING AND ANALYSIS

### **Data analysis plan, including statistical methodology and planned tables and figures**

SAS 9.3 (Cary, NC) as well as the WHO drug efficacy tools provided at <http://www.who.int/malaria/toolsformonitoring.html> will be used for data management and analysis. Data will be analyzed using two methods: **per protocol analysis**, where patients who were withdrawn from the study or who were lost to follow-up are excluded, and **survival analysis**, where all enrolled patients are included in the analysis until the last day before drop-out. In addition to voluntary withdrawals or treatment non-compliance, patients will be considered for the analysis as withdrawn if the PCR results are unclassifiable.

The final analysis will include:

- A description of the patients screened, and the distribution of the reasons for exclusion.
- A description of the patients included in the study.
- The proportion of patients lost to follow-up or withdrawn and the distribution of reasons for withdrawal.
- The proportion of treatment failures in each Pv arm at day 28 and day 42 with 95% confidence intervals using both methods of analysis.
- Frequency of side effects, severe malaria, anemia, and hospitalizations by treatment arm.
- Comparison in absolute means and relative changes in hemoglobin concentration during follow-up after treatment
- Comparison of number of recurrent parasitological vivax episodes after initial parasite episode.

**Data collection:** Data will be collected and recorded at the health facility by one of the trained staff members. All data entry forms will be checked for completeness. Laboratorians may complete brief reports on laboratory findings to share with clinicians who will transfer these results to the case report form of the appropriate patient, the laboratory results will be entered into an Excel database.

**Information management and analysis software:** Microsoft Excel (Redmond, Washington) will be used for double entry of laboratory data and clinical data. SAS 9.3 (Cary, NC) will be used for data analysis.

**Data entry, editing, handling, storage and disposition:** Some open-ended data including the names of specific drugs or diagnoses will be coded prior to data entry. A list of standard codes for these fields will be developed by hand once collection of data is complete. All forms will then be coded and checked by 2 different team members.

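### The no-PQ arms as analysed mix randomised G6PD-normal patients with a few non-randomised G6PD-deficient patients; the expected bias is small, but it is one-sided and easily avoided

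*Protocol*

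**What the plan says.** **Allocation.** The Intervention or treatment section says: "Once G6PD results are available, those testing normal will be randomized to PQ or no PQ". Laboratory Evaluations, item 4, repeats the restriction and adds for the others: "Those found to be G6PD deficient will remain in either the AL or CQ alone arms". Those are the same named arms that hold the randomised controls.

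**Eligibility and withdrawal.** G6PD deficiency is not among the ten exclusion criteria or the withdrawal criteria.

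**Analysis sets.** The data analysis plan describes a survival analysis "where all enrolled patients are included in the analysis until the last day before drop-out". It also describes a per-protocol analysis that removes withdrawn patients (including non-compliance and unclassifiable PCR) and those lost to follow-up. Neither set refers to G6PD status or to whether a patient was randomised.

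**Comparisons.** The primary outcome contrasts AL with AL+PQ and CQ with CQ+PQ at day 28/42. The safety endpoint is: "Change in hemoglobin concentration within 7 days of start of treatment in PQ compared to the no PQ arm". Adverse events and 12-month recurrences are also compared between arms.

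**Aim.** The last paragraph of the Introduction frames the PQ question as one about patients who are not G6PD deficient, to be answered by a randomised trial.

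**The concern.** A comparison of PQ with no PQ is protected by randomisation only if both sides come from the patients who were randomised. Here the control side also takes in everyone who could never have been assigned PQ. Any systematic difference between deficient and normal patients then enters the contrast in one direction, and it does not shrink as the sample grows.

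The hemoglobin comparison deserves most care, because G6PD status is the characteristic the protocol itself links to hemolysis. If deficient patients had a worse hemoglobin course on AL or CQ alone, the control arm would look worse and PQ safer than it is. If their day-42 success were lower, the benefit of PQ would be overstated. Counts of uncommon events, such as the hemoglobin drops above 2.4 g/dL that trigger further G6PD genotyping, could also be moved by a few patients on one side.

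**Working it through.** **Inputs from the protocol.** Deficiency prevalence 0.5-2.9% (Intervention or treatment). From Sample size determination: 120 patients per treatment, hence 240 per blood-stage drug; day-42 success 68% on CQ alone and 87% with PQ; 97 per group at alpha 0.05 and 118 at alpha 0.025; 90% power; two-sided pooled Z test.

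**Assumed, not in the protocol.** How far deficient patients who receive no PQ differ from normal patients in hemoglobin change or day-42 success. Ranges are shown.

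**1. The plan's own sample sizes.** n = [z(1-α/2)·√(2p̄(1-p̄)) + z(0.90)·√(p1(1-p1)+p2(1-p2))]² / (p1-p2)².
- 68% vs 87%, alpha 0.025: 117.6, so 118, as stated.
- 68% vs 87.2% (the unrounded result of a 60% reduction, 1 - 0.32 × 0.4), alpha 0.05: 97, as stated. The rounded 87% gives 100.

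**2. Number of deficient patients per drug.**
- 240 × 0.005 = 1.2 and 240 × 0.029 = 6.96.
- Share of a 120-patient no-PQ arm: 1.2/120 = 1.0% and 6.96/120 = 5.8%.
- If 240 are enrolled and the normals split equally (a ratio the protocol does not state), the upper share is 6.96/(116.52 + 6.96) = 5.6%.
- Chance of at least one among 240: 1 - 0.995^240 = 70% and 1 - 0.971^240 = 99.9%. Some mixing is likely even at the low end.

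**3. Shift in mean hemoglobin change of the no-PQ arm** = share × assumed difference.

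| Assumed difference | 0.5% prevalence | 2.9% prevalence |
|---|---|---|
| 0.5 g/dL | 0.005 | 0.03 |
| 1 g/dL | 0.01 | 0.06 |
| 2 g/dL | 0.02 | 0.12 |

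**4. Shift in the day-42 control success rate** = share × assumed difference. The rejection rate is that of the pooled Z test at nominal 0.05, with both randomised groups at 68% and 120 per arm.

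| Deficient patients' success | Shift at 0.5% | Shift at 2.9% | Rejection rate at 2.9% |
|---|---|---|---|
| differs by 10 points | 0.1 points | 0.6 points | 0.051 |
| differs by 20 points | 0.2 points | 1.2 points | 0.054 |
| all fail (68 points lower) | 0.7 points | 3.9 points | 0.091 |
| all succeed (32 points higher) | 0.3 points | 1.9 points | 0.060 |

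At nominal 0.025 and 2.9% prevalence, the two extreme rows give 0.052 and 0.031. The planned difference is 19 points.

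**5. Cost of leaving deficient patients out**, 68% vs 87%, before dropout.
- Randomised controls: 120 - 1.2 = 118.8, down to 120 - 6.96 = 113.0.
- Power at alpha 0.025: 90.6% with 120:120; 90.5% with 118.8:120; 89.8% with 113.0:120. If both arms fell to 116.5 instead, it would be 89.7%.
- Power at alpha 0.05: 94.6%, falling to 94.0% at worst.
- Enrolment needed to randomise 240 per drug: 240/0.995 = 241.2, so 242, up to 240/0.971 = 247.2, so 248.

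**The case against.** **Nothing material is at risk.** Under moderate assumptions the shift is at most 1.2 points against a planned 19, and the rejection rate at most 0.054. Larger effects need every deficient patient to fail or every one to succeed, and nothing in the protocol supports either. This stands, and it makes the point minor.

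**The comparison is still randomised.** A reader might infer that randomisation is lost. The documents do not support that. All of each PQ arm and about 94-99% of each no-PQ arm are randomised, and Annex VI places G6PD testing before randomisation, so the randomised subset can be recovered.

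**No mechanism is documented.** The protocol ties deficiency to hemolysis under PQ, which these patients do not receive. It nowhere says that their hemoglobin change or recurrence differs on AL or CQ alone. The endpoint is also a change, so a baseline difference alone does not shift it. This stands: the bias is possible, not shown.

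**Deficient patients use up control places.** A reader might infer this too, but the sample size section gives no rule for counting them. With 240 enrolled and equal splitting, both randomised arms would shrink.

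**This belongs in the analysis plan, and single-arm estimates need these patients.** The first part holds only in part: the protocol itself fixes both arm membership and the analysis sets, and read together they pool these patients. The second part stands. The protocol also wants failure proportions by arm, and deficient patients on AL or CQ alone can properly contribute to those.

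A separate conflict does not change the result. One section says "All patients will be randomized to receive AL or CQ", while another says "Patients testing smear positive for Pv will receive AL, at one site and CQ at the other site". These need reconciling, but under both, PQ is randomised only among G6PD-normal patients.

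**Conclusion.** The point holds as a minor one. Followed as written, the protocol puts non-randomised, test-selected patients on the no-PQ side only: about 1 to 7 per drug, or 1-6% of a 120-patient arm, at its own prevalence. The expected distortion is 0.01-0.06 g/dL for an assumed 1 g/dL difference in hemoglobin change, and 0.1-1.2 points at day 42 for an assumed 10-20 point difference in success. These sizes rest on the 0.5-2.9% prevalence applying at the study sites and on differences that the protocol does not give. The case for acting is that the departure from randomisation is known in advance, runs one way, conflicts with the stated aim for PQ, and can be removed at almost no cost. Settling it beforehand also avoids choosing the analysis set after the results of an open-label trial are visible.

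**What to change.** - In Laboratory Evaluations, item 4, state that G6PD-deficient patients are followed on AL or CQ alone but are not members of the randomised arms. No patient's treatment changes.
- In the data analysis plan, state that every PQ versus no-PQ comparison (day 28/42 failure, 12-month recurrences, hemoglobin, adverse events) uses randomised G6PD-normal patients only, in both the per-protocol and the survival analysis.
- Report deficient patients descriptively as a separate non-randomised group. They may still contribute to single-arm AL or CQ efficacy estimates, if labelled as such.
- State the 120 per arm as randomised patients.

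**Cost.** A few sentences. Up to about 7 patients per drug leave the comparison, with the negligible power loss shown above. If 240 randomised patients per drug are wanted, enrolment rises to about 242-248.
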